### **Child Wellbeing**

*Paediatrics Quality of Life (PedsQL; Varni, Katz, Seid, Quiggins, & Friedman-Bender, 1998).*

The PedsQOL is a brief 23 item measure which assesses health-related quality of life in children and adolescents across four dimensions. These dimensions, as delineated by the World Health Organisation include Physical, Emotional, and Social and School functioning. A Total Score, a Physical Health Summary Score and Psychosocial Health Summary Score are derived. The inventory takes approximately four minutes to complete. The inventory has a child self-report and parallel parent proxy report format for ages 5-7, 8-12, and 13-18 years, which can be self-administered except ages 5-7 which has an interview format. Items are scored on a five-point Likert scale, ranging from 'never a problem' to 'almost always a problem.' The child self-report for ages 5-7 is simplified for a three-point Likert scale. An example item from the child report is "It is hard for me to walk more than one block". A higher PedsQL score indicates a better quality of life. Internal consistency for the Total Scale Score ( $\alpha = 0.88$  child, 0.90 parent report), Physical Health Summary Score ( $\alpha = 0.80$  child, 0.88 parent), and Psychosocial Health Summary Score ( $\alpha = 0.83$  child, 0.86 parent) have been reported to be acceptable ((Varni et al., 1998). Reported to be responsive to clinical change over time. The PedsQL distinguished between healthy children and paediatric patients with acute or chronic health conditions.

### **9.3.3 Child Psychopathology**

*The Brief Infant Toddler Social Emotional Assessment (BITSEA; Briggs-Gowan & Carter, 2002).*

The BITSEA will be used as a measure of parent perceptions of their infant or child's difficult behaviours and social-emotional problems. This is a questionnaire for infants that are between 12 and 36 months old, and is therefore an alternative to the SDQ for the infant cardiology group. The BITSEA consists of 42 items, which fall into seven domains: internalizing, externalizing, dysregulation, competence, social relatedness, maladaptive, and atypical. Items are rated on a 3-point scale (0=not true/rarely, 1=somewhat true/sometimes, 2=very true/often), with a higher score suggesting better functioning. An example of an item is "Your child: Hits, bites or kicks you". The BITSEA has good internal consistency and inter-rater reliability, and excellent test-retest reliability (Briggs-Gowan, Carter, Irwin, Wachtel, & Cicchetti, 2004). Internalising, externalising and dysregulation subscales will only be administered.

*OR (depending on age of child)*

*Behavior Assessment System for Children, Second Edition (BASC-2; Reynolds & Kamphaus, 2004)*

*The BASC-2 measures maladaptive and adaptive behaviours and self-perceptions of children. The parent rating scales were utilized according to the child's age, and*

consist of 134-items for children aged 2-5 years, and 160-items for children aged over 6 years. Respondents rate how the child has behaved in the last several months (e.g. 'is easily upset'; 'has trouble making new friends'), on a 4-point scale from "never" to "almost always". The BASC-2 has nine clinical scales, including Hyperactivity, Aggression, Conduct Problems, Anxiety, Depression, Somatization, Atypicality, Withdrawal, and Attention Problems, and three adaptive scales including Adaptability, Social Skills, and Leadership. There are also four composite scores including Externalizing Problems, Internalizing Problems, Behavioral Symptoms Index, and Adaptive Skills. The BASC-2 has good psychometric properties, with established validity, and internal consistency estimates ranging from the middle .80s to middle .90s (Tan, 2007).

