### Eligibility Criteria

#### Inclusion Criteria

To be eligible to participate parents must meet all of the following criteria:

1. Parents must have a child aged between zero and eighteen years during their first presentation treatment for a SCII (cancer, cardiac disease or who have been admitted to hospital in the PICU department)
  - Cardiac – child required surgery within the 1st month of life. This decision was made following consultation with the Head of Cardiology who recommended that we target this group of parents as they are more likely to be traumatised compared to other parents of children with cardiac disease.
  - Cancer – all cancer types
  - PICU – child's stay at PICU must be greater than or equal to 48 hours
2. Parents may be male or female

- 313 3. Both mothers and fathers can participate together or individually, however the  
314 eligible parent must take part
- 315 4. Parents must have an active and current parenting role with the child (defined  
316 as the person(s) who perceives that they have an active parenting role)
- 317 5. Parents must be able to comply with the study intervention and assessment  
318 protocols. This will be determined by the researcher during registration contact  
319 with the parent
- 320 6. Parents may have multiple children diagnosed with an SCII
- 321 7. Parents must be over 18 years

322  
323

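### The protocol reads the BITSEA problem subscales in the wrong direction, and assigns the instrument to cardiac infants who, on the stated schedule, are too young for it at both between-arm visits

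*Protocol*

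**What the plan says.** Protocol section 9.3.3 (Child Psychopathology) introduces the BITSEA as a measure of "parent perceptions of their infant or child's difficult behaviours and social-emotional problems". On scoring it says: "Items are rated on a 3-point scale (0=not true/rarely, 1=somewhat true/sometimes, 2=very true/often". It then describes the scale "with a higher score suggesting better functioning". Its example item is "Hits, bites or kicks you". Of the seven domains listed, one of which is competence, it keeps three: "Internalising, externalising and dysregulation subscales will only be administered". No reverse scoring is mentioned.

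On age, the section says "This is a questionnaire for infants that are between 12 and 36 months old", and for that reason makes the BITSEA the alternative to the SDQ for the infant cardiology group. The SDQ appears nowhere else in the battery. The other option, chosen by the child's age, is the BASC-2, whose youngest form is for 2 to 5 years.

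Under Inclusion Criteria, a cardiac family qualifies only if the "child required surgery within the 1 st month of life". The Child Wellbeing section describes the PedsQL as having a child self-report and a "parallel parent proxy report format for ages 5-7, 8-12, and 13-18 years", and says a higher PedsQL score means better quality of life.

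Table 2 (section 8.3) schedules child wellbeing and child psychopathology at T2 (week 20) and T4 (week 30), the two time points at which the arms are compared. T5 (week 58) is for intervention families only.

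**The concern.** There are two separate faults.

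**Direction.** The stated reading contradicts the item coding, the example item and the choice of subscales in the same paragraph. An analyst who follows it would describe a rise in problem behaviour under TAB as an improvement, and a fall as harm. Because the PedsQL is correctly described as higher is better, the two child outcomes would also be read as pointing the same way when they point in opposite ways.

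**Age.** The infant cardiology group is given the BITSEA on the strength of an age range that this group does not reach at T2 or, on the stated schedule, at T4. Cardiac is one of three randomisation lists, set up partly to allow separate analysis by illness group. For that stratum the planned between-arm comparison of child psychopathology has no instrument within its stated age range.

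**Working it through.** **Direction.** Let the administered subscales hold k problem items, each scored 0, 1 or 2.
- No problem endorsed: score = 0 × k = 0.
- Every problem rated very true: score = 2 × k, the maximum.

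The score therefore rises with problems. If the TAB minus wait-list mean difference is positive, TAB children have more problems, whereas the stated reading calls that better functioning. The difference, its standard error, its p-value and the size of Cohen's d are the same under either reading. Only the verbal conclusion changes.

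**Age on the stated schedule.** Inputs:
- Surgery at 0 to 1 month of age (Inclusion Criteria).
- Screening, which is week 1, within four weeks of diagnosis (section 8.1). I take 0 to 4 weeks after diagnosis or surgery.
- T2 at week 20, T4 at week 30, T5 at week 58 (Table 2).
- One month = 365.25 / 12 / 7 = 4.35 weeks.

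Age at a visit = age at week 1 + (visit week − 1). Age at week 1 runs from 0 to 4.35 + 4 = 8.35 weeks.

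| Visit | Youngest | Oldest |
|---|---|---|
| T2 | 19 weeks = 4.4 months | 8.35 + 19 = 27.3 weeks = 6.3 months |
| T4 | 29 weeks = 6.7 months | 8.35 + 29 = 37.3 weeks = 8.6 months |
| T5 | 57 weeks = 13.1 months | 8.35 + 57 = 65.3 weeks = 15.0 months |

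The stated lower limits are 12 months (BITSEA), 24 months (BASC-2) and 5 years (PedsQL forms described). Every cell for T2 and T4 lies below all three.

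**Late-recontact case.** Section 6.1 allows recontact at 3 to 6 months. Take surgery at 1 month, recontact 6 months later, and T4 ten weeks (10 / 4.35 = 2.3 months) after T2. The wait for a group to form is not given, so it is an assumption shown as a range.

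| Assumed wait | Age at T2 | Age at T4 |
|---|---|---|
| 0 months | 1 + 6 = 7 | 7 + 2.3 = 9.3 |
| 1 month | 8 | 10.3 |
| 2 months | 9 | 11.3 |
| 3 months | 10 | 12.3 |

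Only the combination of the latest recontact and a wait of about 3 months brings a child to 12 months at T4, and T2 is then still out of range.

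**The case against.** **The BITSEA contrasts are not reversed.** A reader might infer that the sign of every BITSEA comparison is wrong. The documents do not support that. The coding is coherent, no recoding is instructed, and section 11.3 compares group means by GEE with no directional test or responder rule that uses the faulty sentence. The objection stands: the fault is in the interpretation only.

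**The two faults limit each other.** If cardiac infants fall outside the BITSEA range, valid T2/T4 scores affected by the direction error come from cancer and PICU children aged 12 to 36 months who are given the BITSEA. That is right. The protocol gives no age distribution, so their number cannot be sized.

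**Not every cardiac child need be under 12 months at T4.** A reader might infer that even recontact at 6 months leaves them all below the limit. Section 8.2 starts a group only when at least five parents have been randomised to TAB, so a wait of unstated length is possible, and about 3 months would be enough. That objection also stands. It does not rescue T2, and it departs from the typical randomisation at three to four months after diagnosis.

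**The PedsQL text lists forms without saying that no others are used.** A reader might infer that no PedsQL score can be valid under 5 years. The protocol does not say so; it needs clarifying.

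**The result may be missing rather than invalid scores.** Section 9.3.3 chooses the instrument by the child's age, and section 11.2 leaves parents with too little subscale data out of that analysis. This is possible, but the protocol also names the infant cardiology group as BITSEA users, so it does not settle which will happen.

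**T5 falls in the BITSEA range.** It does, but for intervention families only and without an in-range baseline, so it offers no between-arm comparison.

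**Conclusion.** Both faults hold as errors in the text.

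The direction statement is wrong for the three subscales used. It leaves estimates and p-values alone but would reverse the conclusion drawn from any BITSEA score.

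On the stated schedule, neither the BITSEA nor the BASC-2 covers the cardiac stratum at T2 (4.4 to 6.3 months) or T4 (6.7 to 8.6 months). This rests on reading week 1 as falling within four weeks of diagnosis or surgery. The T4 part could fail for some children under late recontact plus a wait of about 3 months. The stratum is one of three lists of 26 spaces, so 26 / 78 = one third on that layout; the actual share is not known. Eligibility starts at age zero, so cancer and PICU infants under 12 months have the same gap. For the PedsQL the gap is conditional: it applies unless forms for children under 5 are used.

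These are secondary outcomes. The PCL-5 comparison and its sample size are untouched. The correction is worth making because it is cheap and the text would otherwise mislead the analyst.

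**What to change.** 1. In section 9.3.3, state that higher BITSEA internalising, externalising and dysregulation scores mean more problems.
2. Correct the statement that the BITSEA serves the infant cardiology group, so that it no longer applies at T2 and T4. Remove or explain the reference to the SDQ.
3. Restrict the T2/T4 child psychopathology comparison to children within each instrument's stated age range, with one rule for the 24 to 36 month overlap of the BITSEA and the BASC-2.
4. For children below those ranges, either name an age-valid form or declare the child outcome not applicable. Do the same for the PedsQL, saying whether forms for children under 5 are used.

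The cost is protocol wording. Child secondary outcomes would rest on fewer families, and where an outcome is declared not applicable, cardiac parents would have fewer questionnaires to complete. The primary analysis does not change.

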### **Parent Wellbeing**

#### *Parental Psychological Flexibility Questionnaire- Short Form (PPF- SF; Burke, 2009)*

The PPF- short form (Burke, 2009) is a 19 item instrument that measures parental psychological flexibility. The PPF consists of three subscales designed to measure key elements of psychological flexibility: Emotional Willingness, Cognitive Defusion and Acceptance and also provides an overall level of parental psychological flexibility via a Total Score. The PPF was developed in Study 1 of the thesis that the current study is part of. The measure demonstrates adequate psychometric properties, with good validity and reliability for the Total Scale ( $\alpha = .89$ ) and each of the subscales, Cognitive Fusion ( $\alpha = .90$ ), emotional Willingness ( $\alpha = .74$ ) and Acceptance ( $\alpha = .79$ ). An example item is "My emotions get in the way of being the type of parent I would like to be". The items are measured on a 7-point Likert scale from 1 = Never true to 7 = always true.

#### *Five Facet Mindfulness Questionnaire – Short Form (FFMQ-SF; Bohlmeijer, ten Klooster, Fledderus, Veehof, & R., 2011)*

The FFMQ - SF, consisting of 24 items, is a multifaceted measure of a general tendency towards day to day mindfulness. The five facets include Observing, Describing, Acting, Nonjudging of Inner Experience, and Nonreactivity to Inner Experience. Items are rated on a 5-point Likert scale ranging from 1 (never or very rarely true) to 5 (very often or always true). For all facets, higher scores reflect higher levels of mindfulness. The five facets demonstrated adequate to good internal consistency, with alpha coefficients ranging from .75-.87 (Baer et al, 2006).

#### *Valuing Questionnaire (VQ; Smout, Davies, Burns, & Christie, 2011).*

The VQ8 is an 8-item questionnaire assessing the degree to which people live by their values and is broken down into two subscales – Progress (extent to which people felt that they lived their values in the past week) and Obstructed (the extent to which cognitive and emotional barriers interfered with acting out their values in the past week). Respondents answer items on 6 point likert scale from 0 – *not true at all* to 6 – *completely true*. The VQ8 has very good internal consistency for both factors – Progress  $\alpha = 0.90$  and Obstructed  $\alpha = 0.83$

*Acceptance and Action Questionnaire – II (Bond et al., in press).*

The AAQ-II, containing 7 items, assesses psychological flexibility/inflexibility (e.g., acceptance and experiential avoidance) on a 7 point likert scale ranging from 1 (never true) to 7 (always true). Higher scores reflect greater experiential avoidance and immobility and lower scores are indicative of greater action and acceptance. Psychometric testing reported mean alpha coefficient across the six samples tested of .84 (ranging between .78 - .88), and the 3- and 12-month test-retest reliability is .81 and .79, respectively (Bond et al., in press). Findings from these studies indicate that the measure is related to variables to which it is theoretically tied to. For example, higher levels of psychological inflexibility, as measured by the AAQ-II, are associated with greater levels of anxiety, stress, depression as well as overall psychological distress.

*Life Events Questions*

The life events questionnaire was developed by the senior investigators to obtain information about potential psychosocial stressors that participating parents may have experienced in the past 12 months (in addition to their child's serious illness/injury). The questionnaire contains a total of 14 items and asks about job loss and reduced work hours, recent pregnancies, moving home, suffering a serious illness/injury themselves, separation/divorce, or whether they have experienced an event they found traumatic. The parent is also asked to report on their partner. In addition to these items, a final 15th item was included to ask about a history of mental illness in the year prior to their child's illness/injury.

**Parent Psychopathology**

The Depression Anxiety Stress Scale, (P. Lovibond & S. Lovibond, 1995) was included as a measure of the symptoms of depression, anxiety and stress. This 21-item factor requires respondents to indicate how much each item applies to them on a scale of '0 Did not apply to me at all' to '3 Applied to me very much or most of the time. The DASS-21 has been shown to have good internal consistency reliability, with Cronbach's alpha coefficients reported as .88 for the Depression Scale, .82 for the Anxiety Scale, .90 for the Stress Scale, and .93 for the Total Scale (Henry, & Crawford, 2005). The DASS will also be administered at pre, post and follow up one and two.

**Acceptability**

*Consumer Satisfaction Scale (Parenting Research Centre, 2010).*

The CSS is a measure of consumer satisfaction with parent training programs. It assesses the quality of the service provided; how well the program met the parent's needs and changed behaviour, and whether the parent would recommend the program to others. Parents are also prompted to make general comments or suggestions about the program. The instrument is included as a measure of parental perceptions of the program, the information provided by parents will be used to refine and improve the program. This measure will be completed at Time 4 (post program completion) only.

## **11. STATISTICAL METHODS**

### **Sample Size Estimation**

In order to detect a difference of 6.0 (SD: 13.9) points (thought to be a clinically important difference in parents' experience of distress) in the Posttraumatic Stress Disorder Checklist (PCL- 5) measure, between the two treatment arms, with a significance level of 0.05 and power of 0.80, 82 participants will be required per arm. Allowing attrition, we therefore aim to recruit a total of 184

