#### Randomisation Procedures

Eligible parents will be randomised to either the parent intervention group or the W-L group. This will typically occur between three and four months post their child's diagnosis.

Three randomisation lists will be generated, one list per participating department. This will enable separate analysis by illness group as well as an overall exploration of outcomes for families of children with SCII. Each randomisation list will contain twenty six spaces. Participants will be randomly allocated to one of the two treatment arms using The RCH Department, Clinical Epidemiology and Biostatistics Unit (CEBU), computerised randomisation plan generator. This program will randomise each participant to one of the two treatment arms using the method of randomly permuted blocks. The end result will be two randomly allocated treatment arms of equal size divided between three randomisation lists organised according to Hospital Department (Cancer, Cardiac and PICU).

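### The stated 82 parents per arm falls slightly short of 80% power on the protocol's own inputs: 85 to 86 are needed, and the figure treats parents as independent

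*Protocol*

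**What the plan says.** Section 11 of the protocol (Sample Size Estimation) sets the target difference and spread: "In order to detect a difference of 6.0 (SD: 13.9) points" on the PCL-5, the primary outcome. It continues "with a significance level of 0.05 and power of 0.80, 82 participants will be required per arm", and then "Allowing attrition, we therefore aim to recruit a total of 184". It does not state sidedness, an attrition rate, a design effect or any gain from baseline adjustment.

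Other parts of the protocol bear on the figure:

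- **Randomisation Procedures** plans "two randomly allocated treatment arms of equal size", so allocation is 1:1.
- **Inclusion Criteria** says "Both mothers and fathers can participate together or individually", so two parents of one child may both contribute data.
- **Section 8.2** has TAB groups starting at a minimum of 5 parents and holding at most 10.
- **Section 11.3** plans GEE models that allow for correlation within couples. It mentions no correlation within TAB groups and names no baseline covariate for the outcome comparison.
- **The total** is 184 in section 11 and in section 7.6 (Trial Closure). Section 4.3 puts 184 families in each arm, and section 8.2 has 263 parents in the main RCT.

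**The concern.** The paragraph supplies every input that a two-sample calculation needs except sidedness, yet 82 does not come out of it. A reader who repeats the calculation gets a larger number, so the stated power is not what the stated inputs deliver. The recruitment target of 184 is built on 82, so the margin left for dropout is also affected.

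A second gap sits beside the first. The planned analysis treats partners as correlated, and the intervention is given in groups, but the sample size carries no allowance for either and does not say that independence was assumed. What is at stake is how exactly the power is stated and how much loss to follow-up the target can absorb. The trial's viability is not in question.

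**Working it through.** **Inputs from section 11:** difference 6.0, SD 13.9, significance level 0.05, power 0.80. Equal arms come from Randomisation Procedures. Sidedness is not stated; two-sided is assumed here and one-sided is tried below.

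**Reproducing the stated 82.** The normal formula per arm is n = 2 × (1.960 + 0.842)² × SD² / difference².

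- 13.9² = 193.21 and 6.0² = 36, so 2 × 193.21 / 36 = 10.734.
- (1.960 + 0.842)², with unrounded quantiles, is 7.849.
- n = 10.734 × 7.849 = 84.25, rounded up to **85**.
- The two-sample t-test, solved numerically, gives 85.22, rounded up to **86**.

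The stated 82 is not reproduced.

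**Could another reading give 82?**

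| Reading | n per arm |
|---|---|
| One-sided 0.05 | 67 |
| Both inputs at the favourable edge of rounding (6.05 and 13.85) | 82.3, so 83 |
| SD 13.7 instead of 13.9 (normal) | 81.8, so 82 |
| SD 13.6 instead of 13.9 (t-test) | 81.6, so 82 |
| Difference 6.1 instead of 6.0 (normal) | 82 |

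Only inputs other than the printed ones lead to 82.

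**Power at 82 per arm.** The standard error is 13.9 × √(2/82) = 2.171. Then 6.0 / 2.171 = 2.764, and 2.764 − 1.960 = 0.804, which gives power of 78.9%. The t-test gives 78.5%. The shortfall from 80% is 1.1 to 1.5 points.

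**Difference detectable with 80% power at 82 per arm:** 2.802 × 2.171 = 6.08, about 6.1 points.

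**Attrition margin within 184 randomised:**

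- 82 per arm analysed: 1 − 164/184 = 10.9%
- 85 per arm analysed: 1 − 170/184 = 7.6%
- 86 per arm analysed: 1 − 172/184 = 6.5%

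The 10.9% is implied by the two printed figures; the protocol does not state a rate. Keeping 10.9% with 85 or 86 analysed would need 85/0.891 = 95.4, so 96, or 86/0.891 = 96.5, so 97 per arm. That is 192 to 194 randomised. With no loss at all, 92 per arm would have about 83% power (t-test).

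**Sensitivity to correlation.** The document gives no intraclass correlation (ICC), share of couples or within-couple correlation, so every value below is an assumption.

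- *TAB groups.* Only the TAB arm is clustered, so the standard error is 13.9 × √{[1 + (m − 1) × ICC]/82 + 1/82}, where m is the group size.
  - m = 5, ICC = 0.01: standard error 2.192, power 78%.
  - m = 10, ICC = 0.10: standard error 2.614, power 63%.
- *Couples, both partners in the same arm.* The design effect is 1 + share of parents in couples × correlation.
  - Share 20%, correlation 0.2: design effect 1.04, power at 82 about 77%.
  - Share 50%, correlation 0.5: design effect 1.25, power at 82 about 70%.
  - If partners were split between arms, power would not be lost this way.

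**The case against.** The strongest reply is that the proven error is trivial. Power of 78.5% to 78.9% against 80%, and 6.1 points against 6.0, would change no decision about the trial. Inputs printed to one decimal could hide most of the gap: at the favourable edge of rounding the formula gives 82.3, which would become 82 if rounded to the nearest whole number. The point about size stands. The rounding explanation is possible but needs both inputs at their edge and a result rounded down, and it still leaves a printed figure that the printed inputs do not support.

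It is also fair to say that couples are not ignored: section 11.3 plans GEE for them. That deals with the analysis but makes no allowance in the sample size. The share of couples may be limited, since section 11.3 refers to couples in which both partners are eligible and eligibility requires passing the screening cut-offs.

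A reader might go further and infer that the trial really has power in the low seventies or below. The documents do not support that. Those values come entirely from assumed ICCs or couple correlations, and the couple loss also depends on partners sharing an arm, which the protocol does not clearly state. Nor do the documents support the opposite inference, that baseline adjustment restores the power. Section 11.3 names no baseline covariate, and section 11 claims no such gain.

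**Conclusion.** The sample size figure is wrong as printed, by a small amount. For a two-sided test with independent parents, the protocol's inputs need 85 (normal) or 86 (t-test) per arm rather than 82, and 82 gives 78.5% to 78.9% power. This part rests only on the protocol's figures and the two-sided assumption, and a one-sided test does not rescue 82.

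The missing statement about independence is a real omission, but its cost cannot be determined from the document. The 63% to 78% range for group clustering is a sensitivity range and not an estimate.

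It would be too much to conclude that 184 is inadequate or that more parents must be enrolled. It would equally be too much to say that 184 supports 80% power unconditionally: even with independent parents, that holds only if attrition stays within about 6.5% to 7.6%.

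**What to change.** Restate the sample size paragraph in one of two ways, giving the sidedness:

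1. 82 analysed per arm, with about 78.5% to 79% power for 6.0 points and a detectable difference of about 6.1 points at 80% power; or
2. 85 to 86 analysed per arm for 80% power, noting that 184 randomised then absorbs only about 6.5% to 7.6% attrition, against the 10.9% implied by 164/184.

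In either case:

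- State that the figure assumes independent parents, although couples may enrol and TAB is given in groups of 5 to 10. If a sensitivity range is shown, label its ICC and couple values as assumptions, and say whether partners are allocated together.
- Quote power with baseline adjustment only if the baseline PCL-5 score is added to the analysis model, with the assumed correlation given.
- Reconcile the total of 184 (sections 7.6 and 11) with 184 families in each arm (section 4.3) and 263 parents in the RCT (section 8.2).

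The cost is a change of protocol wording and a slightly less favourable statement: either lower power or a narrower attrition margin. Neither option adds parents to the 184. Keeping both 80% power and the implied 10.9% attrition would instead take 192 to 194.
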